### Secondary outcomes

#### Effectiveness of secondary prevention

A composite variable that groups secondary prevention measures: BP (values < 140/90 mmHg), cholesterol (c-LDL < 70 mg/dL), diabetes mellitus (plasma glycosylated hemoglobin < 7%), absolute cessation or no initiation of smoking and weight (body mass index in the range of 18.5-25 kg/m2).

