**Methods/design:**

A randomized, non-pharmacological clinical trial in six primary healthcare centers in Barcelona (Spain) will assess whether a tailored cardiac rehabilitation program consisting of four motivational interviews and visits with family physicians, primary healthcare nurses and a cardiologist, coordinated with the reference hospital, results in better cardiac rehabilitation than standard care. A minimum sample of 284 participants requiring cardiac rehabilitation after acute myocardial infarction will be randomized to a cardiac rehabilitation group with a motivational interview program or to standard primary healthcare. The main outcome will be physical function measured by the six-minute walk test, and the secondary outcome will be the effectiveness of secondary prevention: a composite outcome comprising control of blood pressure, cholesterol, diabetes mellitus, smoking and body weight. Results will be evaluated at 1,3 and 6 months.

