### Participants and eligibility criteria

Potential participants will be PHC patients admitted to the reference hospital due to acute coronary syndrome (diagnostic codes ICD-10: I20-I22) or post-unscheduled cardiac revascularization surgery (code ICD-10: 021x) and discharged to home in the area of the six PHCs. Inclusion criteria will be age > 18 years, indication for CR and voluntary participation. Exclusion criteria will be: (1) acute aortic disease, severe pulmonary hypertension, uncontrolled arrhythmia, decompensated heart failure or significant valvular or congenital heart disease, (2) heart valve and/or interventricular septum surgery, (3) diseases that prevent exercise, (4) osteoarticular diseases that severely limit exercise, (5) severe mental disorder (i.e. schizophrenia, bipolar disorder, major depression or autism, and severe forms of other disorders), (6) cognitive disability, (7) problems of verbal communication and, (8) inclusion in a hospital CR program.

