#### Other variables and factors

Variables are described in Table 3 and tests or instruments and their characteristics in Table 4, including sociodemographic and household characteristics, clinical status, use of health services, disease management, and lifestyle habits and psychological and emotional status.

**Table 3 Tab3:** Description of variables and operationalization

Group	Name of variable/Factor	Operationalization
**Sociodemographic and household characteristics**	Age	Date of birth
	Sex	Male/female/non-binary
	Educational level	Primary education not completed/Primary education/Secondary Education/Vocational studies/University degree or higher
	Main source of income	Employment/unemployment allowance/disability/retirement pension/social aid (financial welfare benefits)
	Household income	Total €
	Profession/job	Job definition
	Residents at home	Number of residents living at household
**Clinical status**	Anthropometry	Weight (kg), Height (cm) and Waist diameter (cm)
	Body Mass Index	Categorized as normal weight, overweight, obesity and severe obesity
	Blood Pressure	Systolic blood pressure/Diastolic blood pressure (mmHg)
	Diagnoses	Diabetes Mellitus, dyslipidemia, hypertension, all as registered in the electronic health record
	Severity of comorbidity	Results of Charlson Comorbidity index
	Cardiac function	Echocardiographic results at discharge, and ejection fraction,
	Early risk stratification	Results of Canadian Acute Coronary Syndrome Score C-ACS
	Blood analysis results	Erythrocyte counts, biochemistry, lipid and hepatic profile, HbA1c (%), Glucose, mg/dL, Total cholesterol, mg/dL, Cholesterol- HDL, mg/dL, Cholesterol-LDL, mg/dL, triglycerides, mg/dL
	Severity of comorbidity	Charlson Comorbidity Index. (0 to 100)
	Sexual functionality	Alterations due to heart disease
	Active pharmacological prescription	Antihypertensives, Antidiabetics, Antithrombotic, Cholesterol-lowering drugs, Gastric protectors, Thyroid hormone therapy, Antidepressants, Bronchodilators, Opioid analgesics, Other
**Use of Health Services**	Visits to health care centers	Hospitalizations in last 6 months/Emergency service and hospital readmission in last 6 months/PHC nurse visits in last 6 months/PHC family physician visits in last 6 months/Cardiologist visits in last 6 months
**Disease management and lifestyle habits**	Adherence to drug treatment	Results of Morinsky-Green questionnaire
	Adherence to physical activity program	Yes/No

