	Alcohol consumed	Systematic Interview of Alcohol Consumption (ISCA)
	Physical activity	IPAQ questionnaire
	Smoking habit	Non-smoker/smoker/ex-smoker (1 year not smoking)
	Patient activation (self-efficacy)	13-item Patient Activation Measure (PAM-13)
**Psychological and emotional status**	Depressive symptoms	Patient Health Questionnaire. PHQ-9
	Cognitive dysfunction screening	Montreal Cognitive Assessment
	Perceived functional social support	DUKE UNC-11 questionnaire
	Depression/anxiety	Hospital Anxiety and Depression Scale (HADS)

**Table 4 Tab4:** Questionnaires and instrument characteristics planned for use in the trial. ISCA: systematic interview of alcohol consumption

Test/Instrument	Variable/ object of measurement	Characteristics/information
**Morinsky-Green** [37, 38]	Adherence of drug treatment	**Structure:** Self-administered, 4 items with a dichotomous answer YES/NO
		**Interpretation**: Informs about the causes of non-compliance. Compliance is considered if 4 questions are correct (No/Yes/No/No)
**Systematic Interview of Alcohol Consumption. ISCA** [39]	Alcohol consumed	**Structure:** Professional administered, 3 items, allows examination of the amount of alcohol consumed, the frequency, and the variation between work-days and weekends in Standard Drink Units
		**Interpretation:** High risk alcohol consumption is considered if > 28 units in men or > 17 units in women
**Canadian Acute Coronary Syndrome Score. C-ACS** [40]	Early risk stratification	**Structure**: Score ranges from 0 to 4 according 4 items scored with 1 if: age ≥ 75 years, Killip class > 1, systolic blood pressure < 100 mm Hg, and heart rate > 100 bpm
		**Interpretation:** Short- and long-term mortality in patients with acute coronary syndrome
**Charlson Comorbidity** [41]	Severity of comorbidity	**Structure:** Professional administered, 19 diseases rated from 1 to 6, total score between 0–37 points. From 50 years of age, one point is added for each decade
		**Interpretation:** Higher scores indicate a more severe condition and worse prognosis, can be categorized to no comorbidity, low comorbidity, and high comorbidity
**Short Form Health Survey. SF-12** [30, 42]	Health-related quality-of-life	**Structure:** Self-administered, 12 items with Likert-type ratings, ranging from 3–6 points
		**Interpretation:** Results can be standardized to a 0–100 range and then summarized in two dimensions: physical component summary and mental component summary

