### Statistical methods

Outcomes will be evaluated at 1, 3 and 6 months. Participant characteristics will be described using central tendency measures: mean or median and variability: standard deviation or interquartile range for continuous variables, and frequencies and percentages for categorical variables. The results of the physical functional capacity and the six-minute walk test will be transformed into units of metabolic equivalent of task (MET) using the equation and conversion table of the American College of Sports Medicine [33]. Between-group differences will be studied using the Student’s t-test for two samples. The magnitude of the effect will be calculated using Cohen's D. The effect of the intervention or standard care will be calculated using the Student’s t-test or Mcnemar’s test for paired samples. A mixed linear regression model will be used to evaluate trends in each arm, adjusting for variables of interest. For the inference analysis, co-variables that correlate (sociodemographic factors) will be used and adjusted analyzes made. In the comparison of multiple hypotheses, adjustment of the level of statistical significance (α = 0.05) will be used to avoid type I errors. All analyzes will made per protocol and intention-to-treat. The analysis will be made using R v3.5.2 [34].

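### Two of the five secondary-prevention targets (HbA1c and smoking) can be met by patients who never had the risk factor, so they measure absence or control and dilute gains in affected patients

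*Protocol article*

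**What the plan says.** The Abstract describes the secondary outcome as "a composite outcome comprising control of blood pressure, cholesterol, diabetes mellitus, smoking and body weight". The section Effectiveness of secondary prevention defines it as "A composite variable that groups secondary prevention measures", with five targets: blood pressure, LDL cholesterol, HbA1c, smoking and BMI. The two at issue are "diabetes mellitus (plasma glycosylated hemoglobin < 7%), absolute cessation or no initiation of smoking". No denominator is given for the HbA1c target, and no rule is given for combining the five.

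Entry requires neither diabetes nor smoking: "Inclusion criteria will be age > 18 years, indication for CR and voluntary participation". Both are recorded. Table 3 lists "Diabetes Mellitus, dyslipidemia, hypertension, all as registered in the electronic health record" and classifies smoking as "Non-smoker/smoker/ex-smoker (1 year not smoking").

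Statistical methods opens its comparison of the arms with "Between-group differences will be studied using" a two-sample t-test. It also plans a mixed linear model with adjustment variables that are not listed, and says that "co-variables that correlate (sociodemographic factors) will be used and adjusted analyzes made". Diabetes and smoking status at admission are not named as covariates.

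**The concern.** A patient who has never smoked and does not have diabetes can meet two of the five targets in either arm, whatever the programme does. If component rates are shown under the label of control, a high figure may mainly reflect how many patients never had the problem. A real improvement in affected patients is then averaged over everyone else and looks smaller than it is.

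This bears on secondary objective (i), which covers changes in risk factors, and on the only secondary outcome that the Abstract names. The question is who is counted towards a target, not where the cut-offs sit.

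**Working it through.** **Figures in the plan.** The protocol states no rate, effect, prevalence or power for the composite, so there is nothing to reproduce. Its sample size calculation concerns the walk test only. From it I take 142 patients per arm and a two-sided 5% level. All prevalences and control rates below are assumptions.

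**Dilution in one component.** Let q be the share of patients with the risk factor and p the proportion of them at target. If unaffected patients always pass:

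- component rate = (1 − q) + q·p
- difference between arms = q·(p_int − p_ctrl)

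With p = 50% under control and 65% under intervention, a 15-point gain:

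| q | Control | Intervention | Difference | Power, all 142 per arm | Power, affected only (n per arm) |
|---|---|---|---|---|---|
| 20% | 90.0% | 93.0% | 3.0 points | 0.15 | 0.20 (28) |
| 30% | 85.0% | 89.5% | 4.5 points | 0.21 | 0.29 (43) |
| 50% | 75.0% | 82.5% | 7.5 points | 0.34 | 0.44 (71) |

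For q = 30%: 1 − 0.30 × 0.50 = 0.850 and 1 − 0.30 × 0.35 = 0.895. Restricting to affected patients raises power modestly and it stays low. The main gain is that the rate means what its label says.

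**Chance imbalance.** The SD of the difference in q between arms is √(2q(1 − q)/142). At q = 30% this is √(2 × 0.30 × 0.70/142) = 0.054, so the 95% range is ±10.7 points. With p = 50% that moves the component difference by ±0.107 × 0.50 = ±5.3 points. This variation is already part of the component's standard error. In 20,000 simulated trials with no effect at q = 30%, the mean difference was 0.0001 and the type I error 0.048.

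**The composite.** The result depends on how the targets are combined. Assumed scenario, independent components: diabetes 30%, smokers 35%; control versus intervention BP 65% vs 70%, LDL 50% vs 55%, BMI 25% vs 27%, and HbA1c and smoking each 50% vs 65% in affected patients.

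- *Count of targets met.* The expected difference is 0.05 + 0.05 + 0.02 + 0.30 × 0.15 + 0.35 × 0.15 = 0.2175 targets. Adjusting for diabetes and smoking at admission lowers the simulated SE from 0.112 to 0.108, about 4%. Power moves from about 0.48 to between 0.51 and 0.52.
- *All targets required.* Adjustment changes essentially nothing: power 0.119 unadjusted, 0.123 adjusted.
- *Share of applicable targets met.* No gain over the plain count: power 0.47 against 0.48.

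**The case against.** **The HbA1c target may be meant for patients with diabetes only.** Control of diabetes presupposes diabetes, and the diagnosis is recorded. This stands in part. Crediting patients without diabetes is the literal reading, not the only one, and a condensed article may leave the scoring to the analysis plan. It does not help the smoking target, whose wording expressly counts not starting.

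**Under an all-or-none rule the point disappears from the composite.** Scoring a non-applicable target as met gives the same result as requiring all applicable targets. This is correct, and it is why the conclusion is confined to the two components and, slightly, to a count score. The article also does not commit to reporting component rates.

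**Adjusted analyses are already planned.** True, so it would be wrong to say that the plan relies on an unadjusted t-test alone, and the t-test is not assigned specifically to the composite. What is missing is the naming of the two baseline variables that decide who passes automatically.

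**Not starting to smoke is a legitimate secondary-prevention state.** This stands. Restricting the composite's smoking target to admission smokers would lose relapse among ex-smokers, so the composite definition should stay.

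**Stronger readings to avoid.** A reader might infer that real gains shrink to about a third. That factor is simply an assumed prevalence near 33%, applied to one component; the documents give no prevalence, and the factor does not apply to blood pressure, LDL, BMI or the whole composite. A reader might also infer that an uneven split of diabetics or smokers invalidates the comparison. It is ordinary randomization noise, already in the standard error.

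**Conclusion.** The point holds in a limited form. The smoking target by its wording, and the HbA1c target on a literal reading, measure absence or control where the Abstract promises control. A gain among affected patients is scaled by the prevalence in each of these two components: 3.0, 4.5 or 7.5 points in place of 15 at assumed prevalences of 20%, 30% or 50%. There is no bias and no inflation of type I error.

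For the composite the cost is small. Under the assumed scenario, adjusting for baseline status lowers the SE by about 4% if targets are counted, and by essentially nothing if all are required. The case for change rests mainly on interpretability and on how cheap the remedy is.

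**What to change.** Keep the composite as defined and make two additions.

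1. In Statistical methods, name registered diabetes diagnosis and smoking status at admission as covariates in the between-arm comparison of the composite.
2. Report two component results in the patients to whom they apply: HbA1c below 7% among those with a registered diabetes diagnosis, and smoking cessation among those smoking at admission. Report relapse among ex-smokers and initiation among never-smokers separately.

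The combination rule should be stated alongside, because the effect of item 1 depends on it.

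The cost is a few lines of wording, settled before the data are analysed. No new data are needed, since Table 3 already includes both variables. The downside is that the two component results rest on fewer patients (about 43 per arm at an assumed 30% prevalence) and show lower control rates, for example 50% vs 65% where the all-patient figures would read 85.0% vs 89.5%. Power for these components stays low, so they are best presented as estimates with confidence intervals.

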#### Psychological status and quality of life

Measured by the Psychological General Well-Being Index (PGWBI) [29] and the generic SF-12 [30].

#### Other variables and factors

Variables are described in Table 3 and tests or instruments and their characteristics in Table 4, including sociodemographic and household characteristics, clinical status, use of health services, disease management, and lifestyle habits and psychological and emotional status.

**Table 3 Tab3:** Description of variables and operationalization

Group	Name of variable/Factor	Operationalization
**Sociodemographic and household characteristics**	Age	Date of birth
	Sex	Male/female/non-binary
	Educational level	Primary education not completed/Primary education/Secondary Education/Vocational studies/University degree or higher
	Main source of income	Employment/unemployment allowance/disability/retirement pension/social aid (financial welfare benefits)
	Household income	Total €
	Profession/job	Job definition
	Residents at home	Number of residents living at household
**Clinical status**	Anthropometry	Weight (kg), Height (cm) and Waist diameter (cm)
	Body Mass Index	Categorized as normal weight, overweight, obesity and severe obesity
	Blood Pressure	Systolic blood pressure/Diastolic blood pressure (mmHg)
	Diagnoses	Diabetes Mellitus, dyslipidemia, hypertension, all as registered in the electronic health record
	Severity of comorbidity	Results of Charlson Comorbidity index
	Cardiac function	Echocardiographic results at discharge, and ejection fraction,
	Early risk stratification	Results of Canadian Acute Coronary Syndrome Score C-ACS
	Blood analysis results	Erythrocyte counts, biochemistry, lipid and hepatic profile, HbA1c (%), Glucose, mg/dL, Total cholesterol, mg/dL, Cholesterol- HDL, mg/dL, Cholesterol-LDL, mg/dL, triglycerides, mg/dL
	Severity of comorbidity	Charlson Comorbidity Index. (0 to 100)
	Sexual functionality	Alterations due to heart disease
	Active pharmacological prescription	Antihypertensives, Antidiabetics, Antithrombotic, Cholesterol-lowering drugs, Gastric protectors, Thyroid hormone therapy, Antidepressants, Bronchodilators, Opioid analgesics, Other
**Use of Health Services**	Visits to health care centers	Hospitalizations in last 6 months/Emergency service and hospital readmission in last 6 months/PHC nurse visits in last 6 months/PHC family physician visits in last 6 months/Cardiologist visits in last 6 months
**Disease management and lifestyle habits**	Adherence to drug treatment	Results of Morinsky-Green questionnaire
	Adherence to physical activity program	Yes/No
	Alcohol consumed	Systematic Interview of Alcohol Consumption (ISCA)
	Physical activity	IPAQ questionnaire
	Smoking habit	Non-smoker/smoker/ex-smoker (1 year not smoking)
	Patient activation (self-efficacy)	13-item Patient Activation Measure (PAM-13)
**Psychological and emotional status**	Depressive symptoms	Patient Health Questionnaire. PHQ-9
	Cognitive dysfunction screening	Montreal Cognitive Assessment
	Perceived functional social support	DUKE UNC-11 questionnaire
	Depression/anxiety	Hospital Anxiety and Depression Scale (HADS)

**Table 4 Tab4:** Questionnaires and instrument characteristics planned for use in the trial. ISCA: systematic interview of alcohol consumption

Test/Instrument	Variable/ object of measurement	Characteristics/information
**Morinsky-Green** [37, 38]	Adherence of drug treatment	**Structure:** Self-administered, 4 items with a dichotomous answer YES/NO
		**Interpretation**: Informs about the causes of non-compliance. Compliance is considered if 4 questions are correct (No/Yes/No/No)
**Systematic Interview of Alcohol Consumption. ISCA** [39]	Alcohol consumed	**Structure:** Professional administered, 3 items, allows examination of the amount of alcohol consumed, the frequency, and the variation between work-days and weekends in Standard Drink Units
		**Interpretation:** High risk alcohol consumption is considered if > 28 units in men or > 17 units in women
**Canadian Acute Coronary Syndrome Score. C-ACS** [40]	Early risk stratification	**Structure**: Score ranges from 0 to 4 according 4 items scored with 1 if: age ≥ 75 years, Killip class > 1, systolic blood pressure < 100 mm Hg, and heart rate > 100 bpm
		**Interpretation:** Short- and long-term mortality in patients with acute coronary syndrome
**Charlson Comorbidity** [41]	Severity of comorbidity	**Structure:** Professional administered, 19 diseases rated from 1 to 6, total score between 0–37 points. From 50 years of age, one point is added for each decade
		**Interpretation:** Higher scores indicate a more severe condition and worse prognosis, can be categorized to no comorbidity, low comorbidity, and high comorbidity
**Short Form Health Survey. SF-12** [30, 42]	Health-related quality-of-life	**Structure:** Self-administered, 12 items with Likert-type ratings, ranging from 3–6 points
		**Interpretation:** Results can be standardized to a 0–100 range and then summarized in two dimensions: physical component summary and mental component summary
**DUKE UNC-11** [43, 44]	Perceived functional social support	**Structure:** Self-administered, 11 items with Likert-type ratings ranging 1 to 5. Scores range from 11 to 55 points
		**Interpretation:** The higher the average score, the greater the perceived social support
**Montreal Cognitive Assessment** [45, 46]	Cognitive dysfunction screening	**Structure:** Professional administered consisting of 12 tasks of the following domains: visuospatial/executive (5 points), naming (3 points), attention (6 points), language (3 points), abstraction (2 points), delayed recall (5 points), orientation (6 points). Total scores range between 0 and 30
		**Interpretation:** A score < 26 might indicate cognitive impairment
**Patient Health Questionnaire. PHQ-9** [47]	Depressive symptoms	**Structure:** Self-administered, 9 items for screening, diagnosing, monitoring and measuring the severity of depression
		**Interpretation:** Scores and cut-points: 5, 10, 15, and 20 represent for mild, moderate, moderately severe, and severe depression respectively
**Hospital Anxiety and Depression Scale (HADS)** [48, 49]	Emotional distress (anxiety and depression)	**Structure:** Self-administered, 14 items (7 anxiety and 7 depression), with Likert-type ratings ranging 1 to 4. Total ranging from 0 to 21
		**Interpretation:** A total subscale score of > 8 points in each of the sub-scales might indicate depression or anxiety
**International Physical Activity Questionnaires (IPAQ)** [50, 51]	Frequency, duration and intensity of activity	**Structure**: Self-administered, 7 questions self-completed. Evaluates: intensity (low, moderate, or vigorous), frequency (days for week) and duration (time for day)
		**Interpretation:** Classifies the level of activity in three categories: low, moderate, and high. Permits individual results to be converted into METs
**Six-minute walk test** [28]	Aerobic capacity and endurance	**Structure:** Sub-maximal exercise test used to assess aerobic capacity and endurance. The distance covered over a time of 6 min is used as the outcome to compare changes in performance capacity
		**Interpretation:** Allows results to be converted from meters to METs. An increase in the distance walked indicates improvement in physical function
**The 13-item Patient Activation Measure (PAM-13)** [52, 53]	Patient activation (self-efficacy)	**Structure**: Self-administered. 13 items 4-point Likert scale. Total scores range from 0 to 100
		**Interpretation**: Scores are converted into Rasch units defining 4 stages of activation: 1. Believes active role is important; 2. Confidence and knowledge to take action 3. Taking action; 4. Staying the course under stress
**Psychological General Well-Being Index (PGWBI)** [29]	Psychological status and quality of life	**Structure:** Self-administered, 22 items, with 6-point Likert scale, and five dimensions: anxiety, depression, positive mood, vitality, self-control and general health. Total score range is from 0–110
		**Interpretation:** Lower scores indicate more severe distress. The three levels of distress are scored as: 0 to 60 reflect severe distress; 61 to 72 moderate distress; and 73 to 110 positive well-being

